**Methods and analysis:**

University students with anxiety and/or depressive symptoms will be randomised to a (1) 7-week iCBT programme (excluding booster session) with therapist feedback, (2) the identical iCBT programme with computer feedback only or (3) care as usual. Participants in the care as usual condition are informed and referred to conventional care services and encouraged to seek the help they need. Primary outcome variables are self-reported levels of anxiety as measured with the General Anxiety Disorder-7 and self-reported levels of depression as measured with the Patient Health Questionnaire-9. Secondary outcomes include treatment adherence, client satisfaction, medical service use, substance use, quality of life and academic achievement. Assessments will take place at baseline (t1), midtreatment (t2), post-treatment (t3), at 6 months (t4) and 12 months (t5) postbaseline. Social anxiety and perfectionism are included as potentially important predictors of treatment outcome. Power calculations are based on a 3 (group) × 3 (measurement: pretreatment, midtreatment and post-treatment) interaction, resulting in an aimed sample of 276 participants. Data will be analysed based on intention-to-treat and per protocol samples using mixed linear models.

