### Statistical analyses

#### Sample size calculation

The power analysis is based on the mixed factors 3×3 interaction difference between the three treatment arms and three time points (premeasurement, midmeasurement and postmeasurement). We anticipate a small interaction effect (Cohen’s f=0.1) at post-treatment based on a recent meta-analysis that focused on the effectiveness of therapist-guided versus computer-guided psychotherapy in treating depression and anxiety.^17^ We determined a statistical power (1-ß) of.8 and corrected alpha of α=0.05. With a two-tailed hypothesis, we need 204 participants per intervention group to be able to detect a statistically significant result. Previous literature has shown that web-based interventions have a relatively high reported range of drop-out in university students, varying between approximately 30% and 40% posttreatment.^20^ Calculating with a dropout rate of 35%, the minimum required total sample for the RCT is N_total_=276 participants (with a ratio of 1:1:1), with 92 participants in each group.

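### The target of 276 does not follow from 204 evaluable participants and 35% dropout (that needs 314, or 315 in equal arms), and the 204 is a total misprinted as a per-group figure

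*Protocol article*

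**What the plan says.** The sample size calculation in the protocol article rests on the interaction of three arms with three time points (pre, mid, post). It states "We anticipate a small interaction effect (Cohen’s f=0.1) at post-treatment", power of 0.8 and a "corrected alpha of α=0.05". It then says "we need 204 participants per intervention group to be able to detect a statistically significant result".

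The section cites post-treatment dropout of roughly 30% to 40% in earlier student trials and settles on the middle of that range: "Calculating with a dropout rate of 35%, the minimum required total sample for the RCT is" 276, allocated 1:1:1 with 92 in each group. The inflation formula is not given. The abstract repeats the target ("resulting in an aimed sample of 276 participants") and gives no power value.

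**The concern.** Two figures in one short paragraph do not agree with what stands next to them.

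- **Inflation.** A dropout rate is a fraction of those randomised, so the evaluable number is divided by one minus the rate. Here it appears to have been multiplied by one plus the rate, which gives too small a total.
- **Unit of the 204.** A requirement of 204 per group cannot lead, after an upward adjustment for dropout, to 92 randomised per group.

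The article presents 276 as the smallest sufficient sample, and its discussion names potentially high dropout as a limitation, especially in the computer-guided and care-as-usual arms. The dropout allowance is the protection against that limitation. If it is too small, a reader will credit the trial with more power among completers than it was sized for, and that affects how a null result is read.

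**Working it through.** **Inputs from the sample size section.** Arms k = 3, time points m = 3, f = 0.1, alpha = 0.05, power 0.80, evaluable number 204, dropout 35% (cited range 30% to 40%), randomised 276 (92 per arm).

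**Assumed, because the article does not state them.** Correlation between repeated measures ρ = 0.5, and sphericity (ε = 1).

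**Step 1: reproduce the 204.** For the within-between interaction, λ = N·m·f²/(1 − ρ), df1 = (k − 1)(m − 1) = 4 and df2 = (N − k)(m − 1), with power taken from the noncentral F distribution.

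- The smallest N with power of at least 0.80 is 202. Rounded up to a multiple of three, it is 204 (68 per arm).
- At N = 204: λ = 204 × 3 × 0.01 / 0.5 = 12.24, df2 = 402, power 0.806.

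So the stated inputs return 204 as a **total**. As a per-group figure it would mean 3 × 204 = 612 evaluable, which exceeds the 276 to be randomised.

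**Step 2: reproduce the 276.**

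- 204 × 1.35 = 275.4, rounded up to 276. Per arm, 68 × 1.35 = 91.8, rounded up to 92, and 3 × 92 = 276.

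This matches the article exactly.

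**Step 3: apply the dropout rate to those randomised.**

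- 204 / (1 − 0.35) = 313.8, so 314. Per arm, 68 / 0.65 = 104.6, so 105, and 3 × 105 = 315.
- Shortfall: 314 − 276 = 38, or 315 − 276 = 39.
- Completers from 276: 276 × 0.65 = 179.4, about 25 below 204.
- Dropout that 276 can absorb: 1 − 204/276 = 26.1%.

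Step 3 uses only the printed 204, 35% and 276, with 204 read as a total. It does not depend on ρ.

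**Step 4: power among completers with 276 randomised (ρ = 0.5, ε = 1).**

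| Dropout | Completers | Power |
|---|---|---|
| 30% | 193 | 0.780 |
| 35% | 179 | 0.744 |
| 40% | 166 | 0.707 |

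At a fixed N of 179, power is sensitive to ρ: 0.654 at ρ = 0.4 and 0.845 at ρ = 0.6. But those correlations would not have produced 204 (they need 242 and 162). If the trial is sized for 80% at any of ρ = 0.4, 0.5, 0.6 or 0.7 and then inflated in the same way, 1.35 × 0.65 = 0.8775 of the required number remains, and completer power is about 0.74 each time.

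**Step 5: power when partial records are kept.** The abstract plans mixed linear models on the intention-to-treat sample. Baseline precedes randomisation, so everyone randomised has the first measurement. I took generalised least squares information for 276 randomised, f = 0.1, compound symmetry with ρ = 0.5, and data missing at random. Dropouts contribute baseline only, or baseline plus the mid-treatment measurement for half or all of them.

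| Pattern of the effect | 30% dropout | 35% dropout | 40% dropout |
|---|---|---|---|
| Linear divergence over the three times | 0.82–0.84 | 0.79–0.82 | 0.76–0.79 |
| Full effect by mid-treatment, then kept | 0.83–0.90 | 0.80–0.89 | 0.78–0.89 |
| Effect at post-treatment only | 0.79–0.80 | 0.76 | 0.72–0.73 |

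At 35% dropout the range is about 0.76 to 0.89.

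**The case against.** The strongest objection concerns the consequence. A reader might infer that the trial's power falls to 74%, or that 80% cannot be reached at any dropout rate in the cited range. The article does not support that. The planned model keeps partial records, and under two of the three effect patterns checked it reaches or passes 0.80 somewhere within the 30% to 40% range. The 74% holds only if every incomplete record is discarded, and only under a correlation and sphericity that the article does not state. The article also does not say in words that 204 counts completers; that is inferred from its being inflated for dropout. This objection stands, and the power figure must carry those labels. It does not rescue the inflation: the section chose to adjust 204 for a 35% loss and claims no offset from partial data. The completer analyses planned alongside would also recover nothing from partial records.

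A second tempting reading takes the per-group wording literally. That would require 612 / 0.65, about 942 randomised, and would make the trial severely undersized. The stated inputs and the 92 per group both contradict it, so it is a wording slip.

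A third is that the abstract is wrong as well. It states a recruitment target and no power, so it is not wrong if 276 remains the target.

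**Conclusion.** The point holds as an arithmetic and wording error in the sample size section. The number 276 comes from multiplying by 1.35. The section's own 204 and 35% give 314, or 315 in equal arms, so the target is 38 to 39 randomised participants short of what the section says it provides. It covers 26% dropout against a cited 30% to 40%. The per-group label on 204 is wrong; it is a total of 68 per arm.

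The cost in power is modest and conditional. Among completers it is about 74% at 35% dropout (78% to 71% over 30% to 40%), given ρ = 0.5 and sphericity. For the planned mixed model it may be smaller or nil, depending on when the effect appears and how much mid-treatment data dropouts supply. The inflation result is firm. The power figures are only as good as those assumptions.

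**What to change.** In the sample size calculation section:

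1. Give 204 as the total evaluable number (68 per group) in place of the per-group wording, and state the correlation and sphericity assumptions behind it.
2. Then choose one of two statements:
   - Keep 276 and say that 35% dropout leaves about 179 completers, with completer-based power of about 74% (78% to 71% for 30% to 40% dropout, assuming a correlation of 0.5 and sphericity). Add that the intention-to-treat mixed model may recover some or all of the loss, depending on the effect pattern and the missing data.
   - Or say that 80% power among completers at 35% dropout needs 314 randomised, 315 in equal arms.
3. Stop describing 276 as the minimum for 80% power at 35% dropout.

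The abstract needs no change if 276 stays the target. Keeping 276 is a text correction with no effect on conduct or analysis; the only downside is a slightly less favourable stated power. Adopting 314 to 315 as the target would mean recruiting 38 to 39 more participants and updating the abstract.

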#### Clinical analyses

Mixed Linear Model analyses will be conducted with SPSS and R.

To get a more realistic picture of the true efficacy of treatment, completer analyses will also be performed for those participants who adhere to the protocol.

#### Predictor analyses

Predictors of treatment outcome will be investigated on an exploratory basis with predefined predictors: social anxiety and perfectionism, baseline symptoms severity, gender, personality factors and comorbidity. Analyses will be conducted using regression analyses, with interaction effects and structural equation modelling.

### Patient and public involvement

A focus group of university students helped with the design of the study. This group also helped with writing the consent letters, the website texts and checked the clearness of all instructions on the online platform. All university students of the UvA will receive an email with the (anonymised) results at the group level when the project is finished.

## Discussion

Even though many university students face mental problems, only relatively few students use available services.^12^ iCBT programmes are easily accessible, flexible and relatively anonymous.^24^ Hence, they might be a good alternative for reaching out to this group^14^. The current study aims to compare the effectiveness of online interventions for elevated levels of anxiety and/or depression in university students enrolled at the UvA: a therapist-guided transdiagnostic iCBT programme, a computer-guided version of the same programme and CAU. Several moderators are included that may potentially amplify or attenuate treatment response and so may provide new knowledge on effectiveness for different subgroups.

Strengths of this study are the use of a transdiagnostic iCBT programme, its large sample size, and the generalisability of the findings since exclusion criteria are minimal (eg, there are almost no exclusion criteria concerning comorbid disorders; we created a Dutch and English version, so that both national and international student can participate). Moreover, the current iCBT programme is flexible, because participants can complete sessions at their own pace and it includes separate modules focusing on related problems (eg, stress, sleep, alcohol use). This flexibility has both strengths and limitations. On the one hand, participants will not feel pressured, they can work on a session whenever they have time do to so, and they have freedom in choosing additional modules that fit their situation. On the other hand, this might result in a different therapeutic process for each participant, which makes it more difficult to compare the different groups. Also, this flexibility makes it more difficult to investigate the effective components of the programme. One way to investigate this is to follow the course of the symptoms by analysing the presession questionnaire. Some participants might find it difficult to stay motivated or decide between the different treatment module options. Therefore, one of the limitations of this study is a potentially high degree of drop out, especially in the computer-guided programme and in the CAU condition.^25^ To minimise drop out, participants receive up to 3 weekly reminders via the messaging function when they are inactive. In addition, we provide all participants with technical support and suicide risk monitoring. Also, there may be a potential confound of ‘feedback length’, as the feedback in the therapist-guided condition is textually longer than the automated feedback in the computer-guided condition. Due to the large sample size but limited human resources, and our priority to maintain the privacy of participants, all measurements are self-reported and may, therefore, be more subjective than clinician-rated reports. Moreover, participants may not report certain information, for example, whether they receive face-to-face treatment or counselling for their complaints during the current study. Finally, our automated study design allows for blinded assessments throughout the intervention, which on the downside may lead to some assessments not being aligned with the intervention phase (eg, ‘midtreatment’ questionnaires being completed before session 4 has been reached.)

In sum, the current trial is unique as it compares two versions of the same transdiagnostic iCBT intervention; a therapist-guided versus a computer-guided version in a large sample that includes a 1-year follow-up. This study will, therefore, improve our understanding of the need of individualised feedback for computer-based interventions. The findings will significantly add to the knowledge on the treatment of depression and anxiety in university students and will give insight into treatment predictors/moderators that may determine why some students benefit and others do not.

## Ethics and dissemination

The current study was approved by the Medical Ethics Review Committee (METC) of the Academic Medical Centre, Amsterdam, The Netherlands (number: NL64929.018.18) and follows all Dutch ethical legislations. Any unintended effects will be reported to the METC committee. All procedures are in accordance with the latest version of the Helsinki declaration and comply to the GDPR rules (2018). All protocol changes will be reported to the ethical committees, and trial participants per email. Active informed consent from participants is asked for the entire procedure. Results of this trial will be published in peer-reviewed journals.
